### Randomisation

Following signature of the IC by the legal guardians of the minors and/or the child’s agreement (if applicable), randomisation to treatment with/without hydroxyzine will be performed. Randomisation will occur in a 1:1 ratio in blocks of 8. The non-blinded nurse will randomise subjects with electronic case record form (REDCap). The sequence will be blinded to all team members.

Accompaniment by clowns ([name] from Fundacion Theodora) will depend on the clown presence/availability on the day of the intervention. An alphabetical code will be assigned to patients assigned to clown accompaniment (A) or not (B).

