### Statistical analysis

#### Sample size

Anxiety in children will be evaluated through comparing m-YPAS score between the moment of induction of anaesthesia and the presurgical moment prior to the entrance to the operating room. The sample size calculated will allow detection of a difference of means of 14.3 points at m-YPAS between the group with parental accompaniment and hydroxyzine (mean: 18; standard deviation (SD): 13.5 points) compared to the group with parental accompaniment only (mean: 32.3; SD: 24.2 points) [4, 24]. With a sample size of 47 subjects in each group, we would have a power of 90%, with a level of significance of 0.025, to detect these differences. The final sample size would be 188 subjects (47 in each group).

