#### Data analysis

The analysis will be performed by protocol and intention to treat. The qualitative variables will be presented with their frequency distribution. The quantitative variables will be summarised with their mean and SD. The quantitative variables that show an asymmetric distribution will be summarised with the median and interquartile range.

Comparison of the baseline characteristics of the four study groups will be performed. The association between qualitative variables will be evaluated by Pearson’s χ^2^ test or by Fisher’s exact test. For quantitative variables, means will be compared with Student’s *t* test for independent groups or with nonparametric test for the quantitative variables if they do not fit a normal distribution.

For the main outcome (POA) and secondary quantitative variables evaluated, a repeated measures analysis of the variance (ANOVA) will be carried out. The Bonferroni correction method will be used for multiple comparisons.

A comparison of means in each time-point and of the interaction between the dependent variable of the analysis (test score) and the study group (inter-subject factor) will be assessed. If any baseline characteristics between groups present clinically relevant differences, the model will be adjusted by those variables. Qualitative variables will be compared between groups using Pearson’s χ^2^ test. The relative risk with 95% confidence intervals will be calculated. If any of the baseline characteristics between groups presents statistically significant and/or clinically relevant differences between the four study groups, odds ratio (ORs) will be estimated using a logistic regression model. For all tests, a significance level of 5% will be accepted. The analysis of the data will be done by the statistical package STATA 12.0.

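### Bonferroni is valid but avoidably inefficient: Holm's step-down procedure holds the same 5% familywise error on the same p-values, never rejects less, and costs one sentence

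*Protocol article*

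**What the plan says.** The Data analysis section plans a repeated-measures ANOVA for the main outcome and the secondary quantitative variables, and continues: "The Bonferroni correction method will be used for multiple comparisons". No step-down version is named, so the ordinary reading is the single-step method. The same section adds: "For all tests, a significance level of 5% will be accepted". It does not list which comparisons form the family. The paragraph that follows mentions comparisons of means at each time-point and an interaction with study group.

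The Sample size section sizes one contrast, hydroxyzine against parental accompaniment only: "detection of a difference of means of 14.3 points at m-YPAS", with inputs "mean: 18; standard deviation (SD): 13.5 points" and "mean: 32.3; SD: 24.2 points". It states: "With a sample size of 47 subjects in each group, we would have a power of 90%, with a level of significance of 0.025". It gives no mean or SD for the clown group or the combination group.

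**The concern.** Single-step Bonferroni tests each of k comparisons at 5%/k, whatever happens to the others. Holm orders the p-values and relaxes the threshold after each rejection, with the same strong control of the familywise error under any dependence. Anything Bonferroni rejects, Holm rejects too, so the choice of Bonferroni can only cost power.

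The article's main objective is whether hydroxyzine and clowns have an additive effect, and the abstract aims to find the best of four options. Both aims lead to several comparisons among four groups, of which only one was sized. If some contrasts are large, such as parental accompaniment only against the combination, they will tend to be rejected early, and Holm then tests the rest at easier thresholds. At stake is power on the unsized contrasts, at no cost in type I error or patients.

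**Working it through.** **1. The plan's own figure.** Inputs from the Sample size section: difference 14.3; SDs 13.5 and 24.2; two-sided level 0.025; power 90%.

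- Average SD = √[(13.5² + 24.2²)/2] = 19.59.
- n = 2 × 19.59² × (2.241 + 1.282)² / 14.3² = 46.6, so 47 per group.
- Standard error at n = 47: 19.59 × √(2/47) = 4.04. Then 14.3/4.04 = 3.54, and power = Φ(3.54 − 2.24) = 90.3%.

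The stated 47 and 90% reproduce with a two-sided 0.025.

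**2. The same contrast in a family of six.** Four groups give six pairs. That all six form the family is an assumption.

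- Bonferroni level = 0.05/6 = 0.0083, critical value 2.638.
- Power = Φ(3.54 − 2.638) = 81.6%. Simulation with Welch tests and the unequal SDs gives about 79%.
- n for 90% power = 2 × 19.59² × (2.638 + 1.282)² / 14.3² = 57.7, so 58 per group.

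**3. Why Holm cannot do worse.** Holm compares the ordered p-values with 0.05/6, 0.05/5, 0.05/4, 0.05/3, 0.05/2 and 0.05, that is 0.0083, 0.0100, 0.0125, 0.0167, 0.0250 and 0.0500, and stops at the first failure. No threshold lies below 0.0083, so every p-value at or below 0.0083 passes. The first step is identical to Bonferroni, so the probability of at least one rejection is the same.

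**4. Size of the gain.** Simulation: 40,000 trials per scenario, normal data, 47 per group, familywise 5%, six pairs. Tests are Welch, or pooled where a common SD of 19.59 is used. Control (32.3) and hydroxyzine (18) means come from the plan in scenarios (a) to (e). All clown and combination values are assumptions, as are the smaller effects in (f). Gains are for true differences not already near 100%.

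| Scenario | Gain, Holm over Bonferroni (points) |
|---|---|
| (a) Clown effect 7.15, additive; SD 24.2 in control, 13.5 elsewhere | 7 to 16 |
| (b) Same means, common SD 19.59 | 4.5 to 8.7 |
| (c) Clown effect 14.3, additive; three SD patterns | 7 to 15 |
| (d) Clown effect 10, additive | 5 to 18 |
| (e) Combination no better than hydroxyzine | 2 to 8 |
| (f) Small effects (5 and 7 points) | 1 to 4 |

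Scenario (a) in detail, Bonferroni then Holm:

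- control v hydroxyzine: 79.1% to 85.9%
- control v clown: 17.9% to 32.3%
- clown v hydroxyzine: 45.3% to 60.9%
- hydroxyzine v combination: 45.2% to 60.7%
- control v combination and clown v combination: above 99% under both

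Across scenarios, the sized contrast at its planned 14.3 points has about 79 to 82% power with Bonferroni and about 81 to 89% with Holm. Holm never rejected less, and its simulated familywise error was at most 4.3%.

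**5. A family of two.** The level 0.025 equals 0.05/2, which would fit two contrasts, though the article does not say so. Taking control v hydroxyzine and control v clown (7.15 points), the first gains 0 to 0.4 points and the second about 9 to 11.

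**The case against.** Bonferroni is valid and conventional, and nothing in the sentence is false or contradictory. That stands: this is inefficiency, not an error, and type I error is protected.

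The family is undefined in the article, and a condensed article may leave it to the full protocol or analysis plan. That stands too. Six pairs is an assumption, and with two contrasts the sized one gains next to nothing. The simulation also uses single-time tests instead of the planned repeated-measures model, and assumes 47 per cell. The article's "Randomisation will occur in a 1:1 ratio in blocks of 8" covers hydroxyzine only; clown presence depends on availability, so equal cells are not assured. These points make the size of the gain uncertain, but not its direction.

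Simple simultaneous confidence intervals match Bonferroni and not Holm. This is a legitimate reason to keep Bonferroni intervals, but it does not require giving up Holm for the tests.

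Some stronger readings are tempting and are not supported:

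- A reader might infer a fixed loss of, say, 5 to 16 points on most contrasts. That range needs assumed clown-group values and a six-pair family; with small effects the gain is mostly below 5.
- A reader might infer that the combination comparisons are expected to show less than 14.3 points. The article says this nowhere.
- A reader might infer that combination v clown loses most. Under additivity, adding hydroxyzine to clown is worth the full 14.3 points, and in scenario (a) that contrast exceeds 99% power either way.

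**Conclusion.** The point holds as a cheap improvement. The plan names Bonferroni where a procedure with the same error control and never less power is available.

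For a family of six pairs, the gain on contrasts not already near 100% is about 5 to 18 points when effects are additive and sizeable, and about 1 to 8 points when effects are small or the combination adds nothing over hydroxyzine. These figures rest on assumed means and SDs for the clown and combination groups, 47 per cell, and single-time t tests.

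Two limits belong with the conclusion. The power to reject at least one contrast is unchanged. A reader might also infer that Holm rescues the stated 90% on the sized contrast; over six pairs it does not, reaching about 81 to 89%. How the family is defined matters at least as much as which of the two procedures is used.

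**What to change.** Replace the Bonferroni sentence with: *Multiple comparisons are adjusted by Holm's step-down procedure at a familywise 5%.* Apply it to every family for which Bonferroni was intended, including any comparisons at individual time-points, and say which comparisons make up each family. Record the change before the hydroxyzine allocation is unblinded; the Trial status section gives 30 December 2019 for the end of recruitment.

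The cost is one sentence, with no extra data and only simple arithmetic on the planned p-values. The downside is in the intervals: report Bonferroni intervals beside the Holm p-values and note that the two may occasionally disagree, since a contrast rejected by Holm can have a Bonferroni interval that includes zero.

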**Methods:**

We propose a randomised double-blind, controlled clinical trial that will evaluate the effectiveness of both interventions (hydroxyzine and clowns), alone or in combination, to reduce pre-operative anxiety (using the modified Yale scale of preoperative anxiety) in children aged 2–16 years undergoing outpatient surgery (*n* = 188).

Subjects will be randomised into two groups – (1) standard procedure (parental accompaniment) combined with placebo or (2) standard procedure combined with preoperative hydroxyzine. After randomisation, they will be divided by chance into two further groups, depending on the presence of clowns on the patient’s surgery day. Control of pre-operative anxiety will be determined in the four groups by a modified Yale scale of preoperative anxiety and cortisol levels. Compliance of children during induction of anaesthesia, time until anaesthesia recovery, presence of postoperative delirium and use of analgesia until discharge will be also assessed. For additional information, the children, parents and healthcare professionals involved in the study will complete a satisfaction survey.

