## Discussion

POA is observed amongst children during their stay in the operative room with a prevalence of 83.3% [23]. Adverse psychological and behavioural changes (decrease in children’s self-esteem and emotional well-being, increased anxiety, sleep disturbances and social isolation) have been observed in a rate of 25% in children during hospital stay and even at 1-year post-discharge [6]. A recent systematic review also identified negative psychological sequelae in children [18].

The search for an ideal premedication drug to reduce POA in children is ongoing. The drugs used as anxiolytics are not exempt of side effects and the studies about this issue are limited to dental procedures [14–16]. One study [15] evaluated hydroxyzine at doses of 0.15 mg/kg, yet the dose proposed in our clinical trial is of 2 mg/kg.

The role of clowns and hydroxyzine in the management of anxiety is controversial as there are studies both for and against them [18–20]. We have not found any study that determines the additive effect on anxiolysis of distracting techniques with clowns and pharmacological treatment, as we propose in our case.

The proposed study has some limitations. The clowns are not always at the hospital; therefore, assignment to this intervention depends on whether they are present or not on the day of surgery. In order to reduce this bias, the healthcare professionals that plan the patient’s surgery will not know when the clowns come to the hospital.

The main objective of this study is the evaluation of POA. Studies that evaluate POA are difficult to perform and interpret, mostly because of the difficulty in assessing anxiety attributable to the surgical act. According to some studies [3, 25], the moment with the maximum rate of anxiety and fear associated with the entire surgical procedure is during anaesthetic induction. Therefore, evaluating the child’s anxiety during anaesthetic induction is very useful to determine whether the strategies used in the presurgical period have been effective in reducing anxiety [26]. That is the reason why in the present study, POA is evaluated in both moments. Most studies on this topic use a presurgical anxiety rating scale, the m-YPAS [23, 24, 26, 27].

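### Only hydroxyzine is randomised, but the analysis uses a single study-group factor that mixes drug with clown-day presence, and hydroxyzine is powered on 47 v 47 instead of all 188 children

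*Protocol article*

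**What the plan says.** **What is randomised.** The Methods paragraph of the abstract names two randomised arms: "1) standard procedure (parental accompaniment) combined with placebo or (2) standard procedure combined with preoperative hydroxyzine". The Randomisation section confirms this and gives the scheme: "Randomisation will occur in a 1:1 ratio in blocks of 8". With 188 children, that is about 94 in each arm.

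**What is not randomised.** Under Randomisation, clown accompaniment "will depend on the clown presence/availability on the day of the intervention". The Discussion lists this as a limitation: "assignment to this intervention depends on whether they are present or not on the day of surgery".

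**What is analysed.** Crossing the two gives group 1 (standard management), group 2 (clown), group 3 (hydroxyzine) and group 4 (both). The abstract says: "Control of pre-operative anxiety will be determined in the four groups by a modified Yale scale of preoperative anxiety and cortisol levels". The Data analysis section specifies a repeated measures ANOVA with Bonferroni correction, and then "A comparison of means in each time-point and of the interaction between the dependent variable of the analysis (test score) and the study group", where study group is the inter-subject factor. No separate hydroxyzine and clown terms are described, nor is a comparison of all hydroxyzine with all placebo children.

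**What is powered.** The Sample size section compares parental accompaniment plus hydroxyzine (mean 18, SD 13.5) with parental accompaniment only (mean 32.3, SD 24.2), that is, group 3 v group 1. It states "With a sample size of 47 subjects in each group, we would have a power of 90" per cent at a significance level of 0.025.

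**The concern.** A four-level group factor asks whether all four means are equal. Randomisation supports a different question, whether hydroxyzine changes anxiety. The answers can differ. If children on clown days differ from the others, because of the clowns or because of the days, the four means differ even when hydroxyzine does nothing. A significant overall group test therefore does not establish a drug effect. The same holds for any pairwise comparison that crosses clown status, such as group 1 v group 4.

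The second issue is efficiency. Children in groups 2 and 4 were also randomised to placebo or hydroxyzine, yet they do not enter the one comparison that was powered. About half the randomised information on the drug is left out of it.

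The third is fit to the main objective, stated at the end of the Background: whether hydroxyzine and clowns have an additive effect. That question concerns the hydroxyzine-by-clown interaction. A single four-level factor contains this contrast but does not isolate it.

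**Working it through.** **Inputs.** From the Sample size section: difference 32.3 − 18 = 14.3 points, SDs 13.5 and 24.2, 47 per group, 188 in total, level 0.025, power 90%. Assumptions: clown and non-clown halves of equal size, with the same SDs and the same hydroxyzine effect in both. The SDs are taken to be those of the outcome compared. Effects of 10 and 7.15 points (half of 14.3) are added to show a range; the plan does not state them.

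**1. The plan's own figure.** Average SD = √((13.5² + 24.2²)/2) = √(767.89/2) = 19.59. With the normal approximation and a two-sided level of 0.025, n = 47 per group and power at 47 is 90.3%, so the stated figure reproduces. A one-sided 0.025 would give 40 per group, so the level must be two-sided. The Welch test with the noncentral t gives 89.15% at 47 per group; that method is used below.

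**2. Standard error of hydroxyzine v placebo.**
- 47 v 47: √(767.89/47) = √16.34 = 4.04 points.
- 94 v 94: √(767.89/94) = √8.17 = 2.86 points.
- Ratio: √2 = 1.41.

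With a common effect and clown presence as a stratum, 2.86 does not depend on an even clown split. Each stratum with n children per arm contributes precision n/767.89, and these sum to 94/767.89, provided the arms stay balanced within each stratum.

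**3. Power at the same level for both (two-sided 0.025, Welch).**

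| True difference | 47 v 47 | 94 v 94 |
|---|---|---|
| 14.3 points | 89% | 99.7% |
| 10 points | 57.5% | 89% |
| 7.15 points | 31% | 59% |

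The difference detectable with 90% power (normal approximation) falls from 14.2 to 10.1 points.

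**4. Which comparisons clown days can move.** In simulated trials at a single time-point (20,000 runs, no hydroxyzine effect, clown-day shifts of 0, 7.15 and 14.3 points), results were as follows.
- The pooled hydroxyzine contrast rejected in 4.8% to 5.0% of trials at a 5% level.
- Group 1 v group 3 rejected in 0.7% to 0.9%, against a nominal 0.83% if six Bonferroni comparisons are assumed. It keeps its level.
- Group 1 v group 4, at the same assumed level, was significant in 19% of trials for a 7.15-point shift and 81% for 14.3, from the clown shift alone.

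**5. The interaction.** Its standard error with 47 per group is √(2 × 767.89/47) = 5.72 points. By the normal approximation, an interaction of 14.3 points has 60% power at two-sided 0.025 and 71% at two-sided 0.05.

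**The case against.** The strongest reply is that hydroxyzine already has valid tests. Group 1 v 3 and group 2 v 4 are randomised comparisons within one clown status, the Bonferroni comparisons can include them, and the simulation shows that 1 v 3 keeps its level. This stands. A reader might infer that the plan has no randomised test of hydroxyzine; the documents do not support that.

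A reader might also infer that clown-day differences badly inflate the main test. In a single-time-point four-group F test at 5% with no drug effect, rejection is 27% for a 5-point shift and 84% for 10 points. Those figures do not carry over to the plan as written. Its interaction is most naturally group by time, and M0 precedes contact with any anxiolytic method, so a clown-day difference that is constant from arrival cancels there. Nor are such rejections false positives of the test itself, because the four means then do differ, possibly through a genuine clown effect. Only the interpretive point survives: rejection is not evidence for the drug.

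It is also fair that this is a condensed article without its statistical analysis plan. The pooled comparison is not described; that is different from saying it will not be made. A four-level factor contains the drug, clown and interaction contrasts, and coding may be settled elsewhere. But the article does fix its model, its factor and its powered comparison, and none of these is by randomised arm.

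Finally, the main objective concerns the combination, so a pooled drug contrast cannot be the only result. This is accepted and shapes the fix.

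**Conclusion.** The point holds as one of precision and interpretation. The described analysis does not follow the randomised factor, and the powered drug comparison uses about half the children randomised. Using all of them cuts the standard error from 4.04 to 2.86 points. At the planned 14.3 points the trial already has roughly its stated power, so the gain there is modest. At smaller true effects it is substantial: about 31 percentage points at 10 points (57.5% to 89%) and 28 at 7.15 points (31% to 59%).

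These sizes rest on equal SDs and a common hydroxyzine effect across clown and non-clown days, on balanced arms within each, and on a simple two-group comparison instead of the full repeated measures model. A larger contrast results if the 47 v 47 test is put at 0.05/6, but the plan never lists six comparisons, so that version is not supported.

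**What to change.** In the Data analysis section, replace the single group factor by three terms, each with its time terms: hydroxyzine as randomised; clown presence as a stratum, labelled non-randomised; and hydroxyzine by clown.

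- **Hydroxyzine.** Test hydroxyzine v placebo in all 188 children as randomised, adjusted for clown presence. State one level: the Sample size section uses 0.025 and the Data analysis section 5%, and these must be reconciled. State how the two strata are weighted. An equal-weight average loses precision if clown days are uneven. With 30% of children on clown days (28.2 and 65.8 per arm), its standard error is √((767.89/28.2 + 767.89/65.8)/4) = 3.12 points, against 2.86 with precision weights.
- **Additive effect.** Use the interaction with its confidence interval, and acknowledge its limited power.
- **Alongside.** Report the hydroxyzine effect within clown and non-clown days, and the four group means. Label comparisons across clown status as non-randomised.

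The cost is wording only, best settled before unblinding. One small downside: if the drug effect differs by clown presence, the pooled figure is an average, which is why the within-stratum effects are shown beside it.

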#### Outcome measures

POA assessment: All subjects included in the study will be filmed at four moments to later evaluate their POA by the m-YPAS scale.Saliva and blood cortisol determination: Patients’ saliva will be collected by Salivette® device at time-points M1 and M2. Likewise, a 5-ml blood sample will be obtained at time-point M3 to determine blood cortisol levels after the induction of anaesthesia.Induction Compliance Checklist: It will be performed by the anaesthesiologists in the operating room.Assessment of anaesthetic recovery with or without presence of delirium using PAEDS (PediatricAnesthesia Emergence Delirium Scale) [21] and assessment of post-anaesthetic recovery in PACU using Aldrete [22].Vital signs on arrival at PACU and every 30 min until the transfer to general ward: heart rate and respiratory rate.Pain Scales: Multidimensional pain scale for children under 3 years old, face pain scale for children aged 4–7 years and Visual analog scale for children older than 7 years old.Need of postoperative analgesia.Time to hospital discharge after leaving the operating room, in minutes.Evaluation on perceived healthcare quality: to fulfil this objective, a self-administered satisfaction survey will be completed by patients and parents/legal guardians after anaesthesia recovery and once hospital discharge is indicated. Healthcare professionals that usually attend children submitted to Major Outpatient Paediatric Surgery and that are involved in the study will complete the survey when the study is finished. The survey used is elaborated following the general criteria established by the Madrid Health Service for the elaboration of citizen satisfaction surveys [23]. Paediatric patients under 5 years old or older patients and parents/legal guardians with cognitive impairment or difficulty in understanding the language, will be excluded from this evaluation.

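### Baseline adjustment depends on the imbalance observed, under two different triggers, instead of being fixed in advance for the M0 score and age

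*Protocol article*

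**What the plan says.** All references are to the protocol article.

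- **Main and quantitative outcomes** (Data analysis): "a repeated measures analysis of the variance (ANOVA) will be carried out". Covariates enter by this rule: "If any baseline characteristics between groups present clinically relevant differences, the model will be adjusted by those variables".
- **Binary outcomes** (Data analysis): "The relative risk with 95% confidence intervals will be calculated", without condition. Then: "If any of the baseline characteristics between groups presents statistically significant and/or clinically relevant differences between the four study groups", followed by "odds ratio (ORs) will be estimated using a logistic regression model".
- **Baseline table** (Data analysis): "Comparison of the baseline characteristics of the four study groups will be performed", using chi-square or Fisher tests for categorical variables and t or nonparametric tests for quantitative ones.
- **Interaction** (Data analysis): "the interaction between the dependent variable of the analysis (test score) and the study group (inter-subject factor) will be assessed".
- **Baseline data available**: Outcome measures says "All subjects included in the study will be filmed at four moments to later evaluate their POA by the m-YPAS scale". Treatment guideline makes the first of these, M0, the baseline state, before contact with any anxiety-reducing method. Demographics lists age, and the inclusion criteria span 2 to 16 years.
- **Allocation** (Randomisation): hydroxyzine is randomised 1:1 in blocks of 8. Clown accompaniment follows clown availability on the day of surgery.

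**The concern.** The article states a rule for adjustment, and it is the rule that is at issue: whether a covariate is used depends on how the groups turn out. Three things follow.

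1. The two triggers differ. Quantitative models respond to clinical relevance alone; binary models respond to significance, relevance or both. One baseline table could therefore adjust one family of outcomes and not the other.
2. For binary outcomes, an adjusted estimate exists only if the trigger fires, and it is then an odds ratio where the default is a relative risk.
3. A prognostic baseline score is worth adjusting for even when the groups are balanced, because it removes residual variance. A rule that waits for imbalance gives this up in most trials.

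The stakes differ between the two factors. For randomised hydroxyzine, precision is lost. For clowns, which are not randomised, adjustment is the main analytic protection against measured confounding, and a trigger can miss moderate imbalance.

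**Working it through.** **The plan's own figure.** Inputs from Sample size: difference 14.3, SDs 13.5 and 24.2, alpha 0.025, power 90%.

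- Pooled SD = √((13.5² + 24.2²)/2) = √383.9 = 19.59.
- n = 2(2.241 + 1.282)² × 383.9 / 14.3² = 46.6, so 47 per group. The stated figure reproduces with alpha taken as two-sided.
- Power at 47 is 90.3% by the normal formula and 89.4% by the noncentral t.

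**Always adjusting for M0.** The residual SD is 19.59 × √(1 − r²), where r is the correlation between M0 and the analysed outcome. The article does not give r, so it is assumed over a range.

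| r | residual SD | n for 90% | power at 47 | detectable difference at 90% |
|---|---|---|---|---|
| 0 | 19.59 | 47 | 90.3% | 14.2 |
| 0.3 | 18.69 | 43 | 92.9% | 13.6 |
| 0.5 | 16.97 | 35 | 96.7% | 12.3 |
| 0.7 | 13.99 | 24 | 99.7% | 10.2 |

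**Randomised contrast, simulated.** 47 v 47, two-sided alpha 0.025, 20,000 trials per cell. Two stand-ins for the trigger were used, both applied to M0: p<0.05, and an observed difference above 0.25 SD as an assumed proxy for clinical relevance. The 0.25 SD column comes from separate runs.

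| r | unadjusted | p<0.05 trigger | 0.25 SD trigger | always adjusted |
|---|---|---|---|---|
| 0.3 | 89.4% | 89.7% | 90.8% | 91.7% |
| 0.5 | 89.3% | 90.3% | 92.4% | 96.2% |
| 0.7 | 89.4% | 91.1% | 94.3% | 99.6% |

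The p<0.05 trigger fires in about 5% of trials and the 0.25 SD trigger in about 22–23%. Type I error for r = 0.3, 0.5 and 0.7 is 0.025, 0.019 and 0.015 under the first, and 0.022, 0.018 and 0.011 under the second. Neither exceeds 0.025.

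**Clown contrast, simulated under no effect.** 94 v 94 (2 × 47 on each side), alpha 0.05, r = 0.5, 8,000 trials per cell. The true M0 imbalance is assumed.

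| Imbalance | Rule | Adjusted in | Mean bias (SD) | Type I error |
|---|---|---|---|---|
| 0.2 SD | never | 0% | 0.10 | 0.106 |
| 0.2 SD | p<0.05 | 27% | 0.05 | 0.056 |
| 0.2 SD | 0.25 SD | 37% | 0.04 | 0.052 |
| 0.2 SD | always | 100% | about 0 | 0.053 |
| 0.3 SD | never | 0% | 0.15 | 0.174 |
| 0.3 SD | p<0.05 | 54% | 0.04 | 0.061 |
| 0.3 SD | 0.25 SD | 63% | 0.03 | 0.052 |
| 0.3 SD | always | 100% | about 0 | 0.049 |

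At 0.3 SD with the p<0.05 trigger, the mean bias is 0.042 SD, or 0.042 × 19.59 = 0.8 points. It all sits in the 46% of trials left unadjusted, where it averages 0.042 / 0.46 = 0.09 SD, or about 1.8 points.

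**Scale for binary outcomes.** Take a relative risk of 0.60. At 30% control risk the treated risk is 18%, and the odds ratio is (0.18/0.82)/(0.30/0.70) = 0.51. At 50% control risk it is (0.30/0.70)/(0.50/0.50) = 0.43.

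**The case against.** **Baseline may already be used.** If the repeated measures ANOVA includes M0 as a time-point, the group-by-time term uses it implicitly. This stands as a caution: the gain above is measured against an analysis that ignores M0. The benefit does not vanish, though. With equal SDs, a change from M0 has variance proportional to 2(1 − r), against 1 − r² with M0 as covariate. The ratio is (1 + r)/2: 0.65, 0.75 and 0.85 at r = 0.3, 0.5 and 0.7. Age would still be uncovered.

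A reader might go on to infer that M0 is an outcome level that dilutes the group effect. The article does not list the time-points entered, and the comparisons it names are at each time-point and through the interaction, not averaged over time.

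**The harm is limited.** Planned power is already 90% unadjusted, and the randomised contrast suffers no bias or error inflation. The Discussion admits the clown limitation and keeps surgery schedulers unaware of clown days. All of this stands. It bounds the size of the point but does not justify a conditional rule where a fixed one costs nothing.

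**A SAP may list the covariates.** It may, but it would have to reverse a stated rule rather than fill a gap.

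**Other readings that go too far.**

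- That chance-significant baseline tests drive the main analysis: the significance trigger is written only for binary outcomes, and three of the four listed demographics are categorical or would be tested as such.
- That the odds ratio replaces the relative risk: the relative risk is unconditional, and nothing says the odds ratio is reported instead of it.
- That measures would differ from one binary outcome to another: the trigger is a property of the groups, so it fires for all binary outcomes or for none.

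**Conclusion.** The point holds as an avoidable weakness in the analysis rule. It is not an error in the sample size.

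- **Randomised hydroxyzine comparison:** loss of precision only. At an assumed r of 0.5, power is about 90% under a significance trigger, 92% under a 0.25 SD trigger and 96% if always adjusted. The gain depends on r for the quantity actually analysed. Sample size describes a comparison between induction and the presurgical moment; if that is analysed as a change, r with M0 could be smaller, and near zero there is little to gain.
- **Clown comparison:** measured confounding below the trigger is left in. The mean bias is 0.03 to 0.05 SD for assumed imbalances of 0.2 to 0.3 SD at r = 0.5, with type I error of 0.052 to 0.061. Adjusting for M0 and age does nothing for unmeasured differences between clown and non-clown days.
- **Binary outcomes:** whether an adjusted result exists, and on which scale, is decided by the baseline table.

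A reader might infer that conditional adjustment inflates the false-positive rate of the randomised comparison. The simulation shows that it is conservative there. Nor does this defect call for a different primary time-point.

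**What to change.** - Name M0 m-YPAS and age as covariates in the analysis of the post-baseline scores, whatever the observed balance.
- Keep the baseline table as description, and drop baseline testing and judged relevance as triggers.
- For binary outcomes, prespecify one adjusted effect measure with the same covariates, for example an adjusted relative risk, and report it in all cases.
- As an editorial correction, write the interaction as group by time. An outcome cannot interact with a factor, and group by time is evidently what is meant.

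The cost is wording and a few degrees of freedom. Both covariates are already collected, and 47 per group remains sufficient.
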